10.Secondary (mechanism) outcome: Beliefs about voices questionnaire—revised (BAVQ-R) [34]◦ One of the modules within GiVE targets beliefs about voices. This measure can assess the degree to which these beliefs are positive or negative, and may be changing during therapy◦ The 14-item version of this measure will be used to capture ‘persecutory beliefs’ and ‘benevolent beliefs’.

11.Secondary (clinical) outcome: Revised Green Paranoid Thoughts Scale (R-GPTS) [35]◦ Interventions that target one specific symptom of psychosis may have an impact upon other psychosis symptoms. This 18-item measure will capture any impact upon paranoid delusions.

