### Sample size {14}

Under simple randomisation, to detect a medium effect size of Cohen’s *d* = 0.5 with 90% power for 5% significance with one baseline measure and two follow-up measures, with correlation between these of 0.6 [38], 37 participants per arm are required. The adjusted standard deviation obtained from this calculation is 0.663 (step 1).

To estimate the power for a design with clustering in one arm only, we used the following parameters: 6 therapists each with a caseload of 8 participants completing follow-up assessments, an intracluster correlation coefficient (ICC) of 0.05 [39], an equally sized group (for maximum efficiency) of 6 × 8 = 48 unclustered participants for the treatment as usual arm (ICC = 0), a 5% significance level, adjusted variance from Step 1, i.e. 0.663, a medium effect size of Cohen’s *d* = 0.5. This resulted in an estimated power of 88%.

We assume 26% attrition so the sample size to be recruited is 96/(1 − 0.26) = 130 participants, i.e. 65 per group implying a caseload of between 10 and 11 participants per therapist over the course of the intervention.

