## Statistical methods

### Statistical methods for primary and secondary outcomes {20a}

Participant flow through the trial will be shown in a chart according to the CONSORT Statement 2010. Baseline sociodemographic characteristics and outcomes will be summarised by trial arm using descriptive statistics appropriate to distribution. The primary analysis will be conducted using a mixed effects model with clustering by therapist in the intervention group only and control participants forming their own clusters of size 1. We will include fixed effects for PSYRATS-AH Distress at baseline, the stratification variable (site) and allocation and a random effect for therapist/control participant and a random effect to account for repeated observations within participants. A small sample correction (e.g. Satterthwaite’s) will be applied due to the small number of therapists. We will report the adjusted difference in mean PSYRATS-AH Distress between arms, its 95% confidence interval and p value at each time point. Statistical significance is set at the 5% level.

Secondary outcomes will be analysed using mixed effects models appropriate to outcome distribution controlling for baseline voice hearing distress (PSYRATS-AH). A detailed statistical analysis plan will be written by the CTU Statistician and Trial Statistician, agreed with the research team and reviewed by the Trial Steering Committee (TSC).

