The full range of outcomes will be investigated in a cost consequences framework and a cost-effectiveness analysis will be conducted. Group mean costs and QALYs will be analysed in line with other outcomes using mixed effects linear regression, taking account of key baseline prognostic factors and clustering, and with QALYs adjusted for baseline utility scores. Cost-effectiveness will be expressed as incremental cost-effectiveness ratios in a fully incremental analysis. In addition, Incremental Net Monetary Benefit at various cost-effectiveness thresholds, accompanied by Cost-Effectiveness Acceptability Curves will be presented. If necessary, nonparametric bootstrapping techniques will be used to characterise uncertainty in skewed outcomes. Cost-effectiveness will also be calculated in terms of cost per unit improvement in the PSYRATS-AH Distress scale. Data gathered during the study will form a basis for potential subsequent economic modelling.

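### The only baseline covariate named for the clinical and mechanism secondary outcomes is the primary outcome's, not each outcome's own; followed as written, this costs precision

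*Protocol article*

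**What the plan says.** Section {20a} of the Protocol article sets out the primary model term by term, with "fixed effects for PSYRATS-AH Distress at baseline, the stratification variable (site) and allocation", plus random effects for therapist (or single control participant) and for repeated observations. The primary outcome is therefore adjusted for its own baseline.

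The secondary outcomes get one sentence: mixed models suited to each outcome's distribution, "controlling for baseline voice hearing distress (PSYRATS-AH". No other covariate is named, and the sentence covers every secondary outcome.

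The same section says "Baseline sociodemographic characteristics and outcomes will be summarised by trial arm", so baseline values of the outcomes will be in the dataset. The Health Economic analysis section has group means analysed "with QALYs adjusted for baseline utility scores", which is own-baseline adjustment for another outcome.

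**The concern.** Most of the secondary outcomes measure something other than voice distress: anxiety and depression, recovery, self-schemas, styles of relating, beliefs about voices, paranoia. An outcome's own baseline is usually its best predictor. Baseline voice distress will usually predict, say, R-GPTS paranoia less well than baseline R-GPTS does. Eligibility also requires a score of 3 or 4 on one of two distress items, which narrows the spread of the named covariate and tends to weaken its correlation with other measures.

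These outcomes carry interpretive weight. HADS is there to show whether any change reflects emotional distress more generally. Of R-GPTS the article says "This 18-item measure will capture any impact upon paranoid delusions". BCSS, Approve and BAVQ-R are the mechanism measures. Wider intervals than the data require make each of these questions harder to answer.

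Randomisation is stratified by site only, so chance differences between arms in these baselines can be expected. Adjusting for a different variable removes little of such a difference.

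**Working it through.** **1. Reproduce the plan's own figures.** Section {14} plans "with 90% power for 5% significance", "with one baseline measure and two follow-up measures, with correlation between these of 0.6", for "a medium effect size of Cohen’s *d* = 0.5".
- Variance factor for the mean of two follow-ups adjusted for own baseline: (1 + 0.6)/2 − 0.6² = 0.80 − 0.36 = 0.44. Its square root is 0.663, the stated adjusted standard deviation.
- n per arm at two-sided 5% (sidedness assumed) = 36.99, so 37 as stated.
- With 6 therapists × 8 completers, 48 controls and ICC 0.05: SE² = 0.44 × (1.35/48 + 1/48). A noncentral t with Satterthwaite df of about 14.3 gives 88.7% power, against 88% stated.

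The planned efficiency therefore rests on own-baseline adjustment with correlation 0.6.

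**2. Inputs for the secondary outcomes.** Let r be the correlation of an outcome's follow-up with its own baseline, and c its correlation with baseline PSYRATS-AH distress. The document gives neither for any secondary outcome; 0.6 is its planning value for the primary. I assume r = 0.5 to 0.7 and c = 0.2 to 0.4.

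**3. Single follow-up.** SE ratio (PSYRATS-AH-only against own baseline) = √[(1 − c²)/(1 − r²)].

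| | c = 0.2 | c = 0.3 | c = 0.4 |
|---|---|---|---|
| r = 0.5 | 1.13 | 1.10 | 1.06 |
| r = 0.6 | 1.22 | 1.19 | 1.15 |
| r = 0.7 | 1.37 | 1.34 | 1.28 |

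At r = 0.6 and c = 0.2 to 0.3 the effective sample fraction is 0.64/0.96 = 0.67 to 0.64/0.91 = 0.70, as if 30 to 33% of participants had been discarded.

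**4. Mean of two follow-ups, as in section {14}.** The factor 0.44 is replaced by 0.80 − c².
- c = 0.2: 0.76/0.44 = 1.73, SE ratio 1.31.
- c = 0.3: 0.71/0.44 = 1.61, SE ratio 1.27.
- c = 0.4: 0.64/0.44 = 1.45, SE ratio 1.21.

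As an illustration, put a secondary outcome with d = 0.5 through the step 1 power calculation (48 per arm, same ICC). Power falls from about 89% to 68% (c = 0.2), 71% (c = 0.3) or 75% (c = 0.4). The trial is not powered on these outcomes, so this shows only the scale of the loss. The loss disappears only if c equals r.

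**5. Chance imbalance.** With 65 per arm the standard deviation of a baseline mean difference is √(2/65) = 0.175 SD. A difference above 0.2 SD in either direction has probability about 25% (33% with 48 per arm).
- Let q be the correlation between the two baselines. If PSYRATS-AH distress happens to be balanced, the own-baseline slope left uncorrected is (r − cq)/(1 − q²). For r = 0.6 and (c, q) = (0.2, 0.3), (0.3, 0.4), (0.3, 0.5) it is 0.59, 0.57, 0.60.
- A 0.2 SD imbalance then carries 0.11 to 0.12 SD into the estimated effect. A one-standard-error imbalance carries 0.175 × 0.6 = about 0.1 SD.
- If PSYRATS-AH distress is instead imbalanced by its expected amount, q times the own-baseline difference, adjusting for it removes cq = 0.06 to 0.15 out of 0.6. Most of the imbalance remains.

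**The case against.** The strongest reply is that one condensed sentence is not a model specification. It does not name allocation, time or the random effects either, and allocation must be in the model, so not being named cannot mean being excluded. A detailed statistical analysis plan is promised and is not shown. This stands in part: a reader might infer that the protocol rules out own-baseline adjustment, and the text does not say so. But the article is not silent on covariates. It names one for all secondary outcomes, and it is the less useful one for most of them. An analysis plan that followed the sentence literally would inherit the loss.

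Two further readings are tempting, and the document does not support them. A reader might infer that site is dropped from the secondary models. Not repeating the stratification factor in a one-line summary is ordinary condensation of the primary model. A reader might also infer that costs get no baseline adjustment, because only QALYs are tied to a named baseline score. The same sentence has costs and QALYs analysed with allowance for baseline prognostic factors, which may include baseline cost; the CSRI is collected at baseline.

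It is also fair to say that the size rests on assumed correlations, that the single-follow-up formula ignores therapist clustering, and that the low end is only 6%. The loss is likely to be smaller for outcomes close to voice distress, such as the other PSYRATS-AH subscales.

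**Conclusion.** The point holds as a weakness in what section {20a} fixes for the clinical and mechanism secondary outcomes. The named covariate is the primary outcome's baseline, while the plan uses own-baseline adjustment for the primary outcome and for QALYs.

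The harm is lost precision, plus conditional bias when an imbalance has occurred. A reader might infer systematic bias; randomisation keeps these estimates unbiased on average whichever baseline is used.

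The 6 to 37% range, and the 19 to 22% and 27 to 31% figures within the assumptions above, depend on correlations that the document does not give. The direction does not depend on the exact values, provided an outcome's own baseline predicts it better than baseline voice distress does. The primary analysis, its sample size and the economic analysis wording are not affected.

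**What to change.** Reword the secondary outcome sentence in section {20a}, and carry it into the statistical analysis plan, along these lines: each secondary outcome will be analysed with a mixed model suited to its distribution, adjusted for that outcome's own baseline score, with the same site term and random effects as the primary model. Baseline PSYRATS-AH distress may stay as an additional covariate.

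If own-baseline adjustment was always intended, this only makes the text say so. The cost is a wording change made before analysis. The baseline values are already being collected, and sample size and conduct do not change.

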### Interim analyses {21b}

N/A. There are no planned interim analyses.

### Methods for additional analyses (e.g. subgroup analyses) {20b}

#### Health Economic analysis

The resource requirements of each arm (GiVE with TAU vs. TAU alone) will be investigated using trial details on the delivery of GiVE and data gathered from participants for TAU. Staff time will be costed using national tariffs, inclusive of oncosts and overheads, [41] materials used in the intervention will be valued at cost to the study. Participants will be asked to complete the Client Service Receipt Inventory (CSRI [29]) at baseline, at the end of the intervention (16 weeks) and at the 28-week follow-up to record primary, secondary and community-based health care, including activity classed as standard care. The CSRI is a well validated instrument for use in mental health settings, that can be customised to individual projects, and which includes recording of social, criminal justice and voluntary sector input, informal caring and private out-of-pocket expenditures. Service use will be costed using national tariffs [41]. Variability in standard care will be explored. Differences in service use between groups will be investigated for indications of potential savings associated with GiVE that might offset the intervention costs.

Health-related quality of life (HRQoL), the primary outcome for the economic evaluation, will be recorded at all three assessment points (baseline, 16 and 28 weeks) using both EQ-5D-5L [36] and SF-12 v2 [37] for calculation of QALYs as the latter may be more sensitive to changes in the psychological status. Variability in findings from EQ-5D-5L and SF-12 v2 will be compared.

The full range of outcomes will be investigated in a cost consequences framework and a cost-effectiveness analysis will be conducted. Group mean costs and QALYs will be analysed in line with other outcomes using mixed effects linear regression, taking account of key baseline prognostic factors and clustering, and with QALYs adjusted for baseline utility scores. Cost-effectiveness will be expressed as incremental cost-effectiveness ratios in a fully incremental analysis. In addition, Incremental Net Monetary Benefit at various cost-effectiveness thresholds, accompanied by Cost-Effectiveness Acceptability Curves will be presented. If necessary, nonparametric bootstrapping techniques will be used to characterise uncertainty in skewed outcomes. Cost-effectiveness will also be calculated in terms of cost per unit improvement in the PSYRATS-AH Distress scale. Data gathered during the study will form a basis for potential subsequent economic modelling.

#### Adherence and competence analysis

Therapeutic drift will be minimised by the structure and detail of the workbook and close supervision of the APs by the Site Leads. Adherence to the workbook will be assessed through APs completing a session checklist at the conclusion of each session. All therapy sessions will be audio-recorded (with the participant’s consent – which will be verbally re-affirmed at the beginning of each therapy session) and a random 10% sample rated for adherence and competence by an independent CBT expert. These recordings will be rated for adherence using the session checklist. In addition to providing an independent assessment of the AP’s delivery of the session content, cross-referencing of the self-report and independently rated checklists will offer insights about the ability of APs to monitor their own performance. Session recordings will also be rated for competence using a version of the Cognitive Therapy Scale-Revised (CTS-R) [28] that has been adapted for use within the training of ‘lower intensity’ therapists within the Improving Access to Psychological Therapies services within Sussex.

#### Development of the model for future implementation

The development of an implementation model will use a Normalisation Process Theory framework [42] and build on the key findings from the process evaluation conducted within the feasibility RCT. Specifically, referring clinicians proposed that the GiVE intervention should be embedded into routine service, and be clearly positioned as a CBT-informed intervention, delivered in close collaboration with both CCs (who could further consolidate and support learning after the completion of the GiVE intervention) and highly trained therapists (who could offer subsequent CBTp, where needed). With this in mind, the development of the implementation model will involve two components. Initially, over a six-month period, a series of stakeholder group consultations will be conducted with policy makers, clinicians and highly trained therapists. We will aim to recruit 8–15 stakeholders including at least 2 each of policy makers, CC referrers and expert therapists. Policy makers will be recruited from the national advisory groups involved in developing new psychological therapy roles. CCs and expert therapy leads will be recruited from study sites. Participants will meet either in person or online. Participants will be invited to take part in an interview where they will review the model and consider approaches to implementation in terms of: coherence with current provision; cognitive participation; collective action; and reflexive monitoring. Interviews will be facilitated by either one (individual) or two (small-group) researchers and guided by a topic-guide based on NPT theory. They will be audio-recorded and recordings saved in a manner that is consistent with study and Trust protocols. Audio recordings will be transferred as soon as possible to secure NHS or University servers. Once transcribed, audio-recorded interviews will be deleted. Data will be analysed thematically using a thematic framework analysis approach [43].

Analysis of the transcripts from the consultations will produce a list of potential components of the model and considerations for implementation. A subsequent Delphi consultation, conducted over three months, will be implemented with these same consultants to reach consensus, especially where there were differences of opinion on the core components of the model derived from the qualitative findings, on which there is a group consensus. An online questionnaire format will elicit ratings of the feasibility and importance, and qualitative feedback on key components of the model. A second round will share key learning from the first round to encourage consensus on the final model. The model will be written-up during the final three months of the proposed study.

#### Evaluation of use and experience of self-help materials

A qualitative evaluation will aim to identify barriers and facilitators that may exist for participants when making use of the self-help resources that comprise the GiVE intervention, namely the CHOICES app, the self-help book [21] and the workbook [22]. An increasing number of psychological interventions for symptoms of psychosis are making use of ‘Therapeutic Resources’ (equipment that facilitates a psychological intervention partially or wholly independent of contact from a therapist). The CHOICES app, the self-help book and workbook are examples of Therapeutic Resources (TR). It is therefore important to know what might help and hinder engagement in using TR such as those within the GiVE intervention. Enablers and barriers to engagement with TR have been identified in other trials (digital TR [44, 45]), and also within the GiVE series of trials (paper-based TR [46]). However, there has been no attempt to explore the experiences of participants when they are offered a suite of both digital and paper-based TRs. This leaves important gaps in knowledge when considering the training and supervision of therapists who are delivering interventions that make use of TR as a core part of the intervention, and the implementation of guided self-help interventions in a psychosis population.

This evaluation will aim to explore the experiences via an opportunity sample of 15 participants who: 1) are allocated to the GiVE intervention arm of the trial; 2) have given consent to be contacted for further research when initially consenting to participate within the trial; and 3) have completed the 28-week assessment. Eligible participants will be identified by the TM and invited to participate in the evaluation by an RA. Eligible participants expressing interest will be contacted by a researcher to obtain informed consent to be part of the qualitative evaluation. After participants have consented, arrangements will be made for an interview to be conducted by telephone or video call. The interview will be guided by a semi-structured interview schedule and transcribed verbatim. Qualitative data will be analysed using Thematic Analysis [47]. All qualitative data analysis will be undertaken using NVivo, a qualitative data analysis software. Participants will be reimbursed £20 in Amazon Vouchers for their contributing to the interview.

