## Assignment of interventions: allocation

### Sequence generation {16a} and Concealment mechanism {16b}

The CTU will set up the online randomisation process. The RAs, the Trial Statistician and the CTU Statistician will be blind to participant allocation. Following the baseline assessment, participants will be randomised, stratified by site, by the TM in permuted blocks of randomly varying length using the online randomisation module of REDCap and allocated to one of the trial arms. The next allocation is only revealed upon request. Further, the permuted blocks make the next allocation almost impossible to guess.

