### Implementation {16c}

The TM will communicate the allocation to the appropriate unblinded members of the research team. An unblinded member of the research team will then contact the participant by telephone to inform them of their group allocation. APs will be notified by the TM about the participants who are allocated to the GiVE arm and will be asked to arrange a first appointment, if possible, within two weeks following the randomisation.

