## Assignment of interventions: Blinding

### Who will be blinded? {17a}

The CTU will set up the online randomisation process. The RAs, the Trial Statistician and the CTU Statistician will be blind to participant allocation. Measures to maintain blinding will include: (1) participants being reminded at the beginning of each assessment interview to not disclose the arm to which they have been allocated; (2) blinded members of the research team being shielded from discussion of participants in forums where the possibility of determining participant allocation could occur; (3) researcher access to electronic health records being restricted; and (4) consideration given to office allocation and all administrative processes of blinded-vs-unblinded members of the research team. ‘Blind’ awareness and education will be promoted throughout the study. To test the success of blinding, the RA who assesses each participant will be asked to guess the allocation group for the participant at the end of the final assessment. Reported breaks in blinding will be recorded.

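### Research assistants declared blind without exception are given the task of inviting participants to an interview open only to the GiVE arm

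*Protocol article*

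**What the plan says.** Two sections of the protocol article, the one on sequence generation and concealment ({16a}, {16b}) and the one on who will be blinded ({17a}), carry the same sentence: "The RAs, the Trial Statistician and the CTU Statistician will be blind to participant allocation". Neither gives an end date or an exception. Section {17a} also shows that RAs assess outcomes, since "the RA who assesses each participant will be asked to guess the allocation group for the participant at the end of the final assessment". It lists measures to protect the blind, one of them being "blinded members of the research team being shielded from discussion of participants in forums where the possibility of determining participant allocation could occur".

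The section on use and experience of the self-help materials plans an opportunity sample of 15 interviewees. Among the conditions are that they "are allocated to the GiVE intervention arm of the trial" and "have completed the 28-week assessment". On who approaches them it says: "Eligible participants will be identified by the TM and invited to participate in the evaluation by an RA". The later contact to obtain consent is given to a researcher, whose blinding status is not stated.

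Elsewhere, contact that reveals the arm goes to other staff. Under Implementation {16c}, "An unblinded member of the research team will then contact the participant by telephone to inform them of their group allocation". The TM carries out the randomisation ("stratified by site, by the TM in permuted blocks of randomly varying length") and so knows the allocations.

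**The concern.** An RA cannot issue an invitation reserved for one arm without learning that the invitee is in that arm. The role declared blind is thus handed a task that unblinds it. This is a conflict between two stated procedures and not a detail lost in condensing the article.

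It deserves attention because participants cannot be blinded to a talking therapy and the primary outcome, the PSYRATS-AH distress subscale, is observer-rated. Assessor blinding is therefore the main protection against detection bias. At stake are the accuracy of the blinding statement and the risk that an assessor becomes better at recognising the GiVE arm in people still to be assessed.

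**Working it through.** The article gives no figure to reproduce here. The check compares the sections, then asks whose data could be affected.

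**1. Is there a conflict?** RAs are blind, with no exception ({16a}/{16b} and {17a}). The inviter is an RA, and the eligible arm is GiVE only (self-help materials section). Each invitation therefore discloses one allocation to an RA. The text does not describe the inviting RA as unblinded or as someone who does not assess. The conflict is on the face of the document.

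**2. How many disclosures?** If the target of 15 interviews is met, at least 15 allocations are disclosed across the trial, and more if some invitees decline. Against 65 participants planned for GiVE, 15/65 = 23% of the arm.

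**3. Can the invitees' own data be affected?** No. Invitation follows the 28-week assessment, which is the last one, and the allocation guess is made at the end of that assessment.

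**4. Could the RA still be assessing others?** The Trial status section gives a start in October 2022 and recruitment and data collection until April 2024. Assumptions: start 1 October 2022, end 30 April 2024, last randomisation 28 weeks before the end, even recruitment.
- First participants reach week 28: 1 October 2022 + 28 weeks = 15 April 2023.
- Time left for assessments after that: 15 April 2023 to 30 April 2024 = 54.4 weeks.
- Recruitment window: 1 October 2022 to 17 October 2023 = 54.4 weeks.
- A 16-week assessment falls after the first week-28 completion if the person was randomised more than 28 − 16 = 12 weeks after the start. Share: (54.4 − 12)/54.4 = 78%.

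Overlap is therefore likely if invitations are issued as participants become eligible. The article does not say when they start.

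**5. Does one known allocation reveal another?** Randomisation is individual, within site, in permuted blocks of varying length whose sizes are not given. I assume sizes 2 to 8 and an even split over three sites: 130/3/54.4 = 0.80 randomisations per site per week. The span of a block of size b is (b − 1)/0.80 weeks. The chance that a block-mate is in GiVE, given one known GiVE member, is (b/2 − 1)/(b − 1).

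| Block size | Span (weeks) | Chance block-mate is in GiVE |
|---|---|---|
| 2 | 1.3 | 0 |
| 4 | 3.8 | 0.33 |
| 6 | 6.3 | 0.40 |
| 8 | 8.8 | 0.43 |

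A disclosure comes no earlier than the invitee's week 28. A block-mate's 16-week rating is still open then only if that person was randomised more than 12 weeks later. Every span in the table is shorter than 12 weeks, so on these assumptions no block-mate's primary assessment is exposed. A later block-mate's 28-week rating could be, slightly.

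**The case against.** The strongest reply is that the blinding claim is about outcome assessment. The design promises blind post-treatment and follow-up assessments, and for every invitee that promise has been kept by the time of the invitation. The article says only that an RA invites; it does not say this is the RA who rates others at the site, or that interviews overlap with follow-up. The shielding measure speaks of discussion in forums, and one invitation is not clearly that. The section on unblinding {17b} also provides for a fresh RA where unblinding occurs at the start of an assessment.

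Much of this stands. The invitees' data are safe, overlap is an inference from the calendar, and the shielding measure is only an approximate fit. It does not remove the conflict. The blinding sentence is not limited to the period before a participant's last assessment, and no text sets the inviting RA apart. The provision in {17b} deals with an assessor unblinded about the person being assessed, which is a different situation.

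Three stronger readings are tempting, and the documents do not support them:
- **That an RA could work out other allocations from a block**, for example in a block of four with both GiVE members known. Block lengths are not given and vary at random, and nothing says RAs know where blocks begin and end.
- **That at least five allocations per site are disclosed.** 15/3 = 5 is an average under an even split. The sample is an opportunity sample with no site quota.
- **That the primary outcome is materially at risk.** The timing in step 5 of the working puts leakage to the 16-week endpoint close to nil.

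**Conclusion.** The point holds as an inconsistency in procedure with a minor residual risk. As written, the invitation step makes the unqualified blinding statement inaccurate. The risk that remains is indirect: an RA probably still assessing others learns some allocations and may hear about the workbook, the app or the therapist, which makes later accidental disclosures easier to recognise. No documented figure allows that to be quantified, and I would expect it to be small.

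This rests on two assumptions: that invitations run alongside follow-up, which the calendar makes likely, and that inviting RAs are drawn from the assessing RAs, which the article leaves open. If either fails, only the wording problem remains. Sample size, power and the planned analysis are unaffected.

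**What to change.** In the section on use and experience of the self-help materials, give the invitation to the TM or another unblinded member of the research team instead of an RA. Alternatively, keep RAs as inviters but state that no invitation is issued until all participants' 28-week assessments are complete.

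The first option costs a few words and moves at least 15 invitations, if the target is met, to staff who already know allocations; the TM already identifies the invitees. The second needs no change of staff but pushes the interviews to the end of data collection, which may strain the timetable and lengthen recall for the earliest participants.
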